#### Primary outcome measure

Healthy behavior: The Health Promotion Lifestyle Profile II (HPLP II) will be used to measure patient’s healthy behavior. The scale was revised by American nursing scientist Walker [31], which mainly includes 6 dimensions and 52 items. The total Cronbach’s *α* coefficient of the scale is 0.94, and the Cronbach’s *α* number of each dimension is 0.79–0.87. Each item is scored by grades 1–4; the higher the score, the better the healthful lifestyle. It will be checked at visits 1, 8, and 9.Readmission rate: In this study, readmission is defined as the readmission caused by cardiovascular problems, including hypertension, angina, arrhythmia, cardiac insufficiency, etc., excluding the cases of readmission due to cold, tumor, and other factors. The readmission will be followed up by telephone for 3 months. The readmission information will be collected at visits 8 and 9.Anxiety: The Self-rating Anxiety Scale (SAS) will be used to measure the anxiety of patients with CHD. The scale was compiled by Chinese professor Zung (1971), there are 20 items on the scale, each item is scored by grades 1–4, and items 5, 9, 13, 17, and 19 are scored in reverse. According to the results of Chinese norm model results [32], the cut-off value of the SAS standard score is 50, of which 50–59 is mild anxiety, 60–69 is moderate anxiety, and over 69 is severe anxiety. The scale has been widely used in China and its validity and reliability have been verified (Cronbach’s *α* 0.82). The anxiety score will be measured at visits 1, 8, and 9.

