#### Withdrawal criteria

Participants who meet the criteria summarized below are withdrawn from the study. The subjects who are withdrawn after randomization will be followed up for outcomes. Reasons for withdrawal will be documented in follow-up records and data will be analyzed using the intention-to-treat (ITT) principle.

All subjects have the right to withdraw for any reasonThose who could not complete the test as required, with serious adverse events and complicationsFailed to have three consecutive telephone connections during the follow-up period at the end of the study

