### Outcome

The primary outcome indicators are healthy behaviors, readmission rate, and anxiety level, and the secondary outcome indicators are psychological capital, subjective well-being, and clinical indicators (including TC, LDL, HDL, blood glucose, body mass index, etc.).

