### Statistical analysis

The Kolmogorov–Smirnov test will be used to test the normal distribution of continuous variables. Continuous variables will be presented by mean ± standard deviation (SD) if they are normally distributed or by median with interquartile range if they are not normally distributed. For the comparison of measurement data between the two groups, a *t*-test of two independent samples will be used for normal distribution data, and the Mann–Whitney *U* rank sum test will be used for non-normal distribution data. The comparison of count data between the two groups will be performed by *χ*^2^ test or Fisher’s exact test. An independent statistics expert will perform statistical analysis in a blind manner. SPSS for windows version 25.0 (SPSS Inc., Chicago, IL, USA) will be used for statistical analysis. The statistical level of significance will be set at *P* < 0.05.

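### The primary readmission outcome does not separate planned from unplanned cardiovascular admissions, and its time window is stated inconsistently

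*Protocol article*

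**What the plan says.** The Outcome section gives readmission primary status: "The primary outcome indicators are healthy behaviors, readmission rate, and anxiety level".

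The section Primary outcome measure defines the event by its cause: "readmission is defined as the readmission caused by cardiovascular problems, including hypertension, angina, arrhythmia, cardiac insufficiency, etc". It then removes other causes: "excluding the cases of readmission due to cold, tumor, and other factors". The words planned, elective, scheduled and staged do not appear in the definition.

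On timing, the same section says "The readmission will be followed up by telephone for 3 months" and, in the next sentence, "The readmission information will be collected at visits 8 and 9". Table 1 places visit 8 at week 12 and visit 9 at week 24. Study design and setting describes a 3-month intervention followed by 3 months of follow-up.

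For the analysis, the Statistical analysis section says "The comparison of count data between the two groups will be performed by" a chi-square or Fisher's exact test. It names no time point for readmission.

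**The concern.** Every participant has had PCI, and the inclusion criteria run from stable angina to myocardial infarction. Some of these patients may leave hospital with a further cardiac admission already booked, such as a staged procedure. That admission has a cardiovascular cause, so it meets the definition, but the intervention has no means of preventing it. Such events arise at about the same rate in both arms. They pull the risk ratio towards 1 and add noise.

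The unclear window adds to this. The outcome could be taken as readmission by week 12, between weeks 12 and 24, or by week 24. Each gives a different event count. With 40 patients per arm and a primary outcome, that choice should be settled before anyone sees the data.

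**Working it through.** **Is there a figure in the plan to reproduce?** Not for readmission. The sample size calculation compares two means (SD 12.68, difference 10.39, two-sided alpha 0.05, power 0.80). The main term is 2 × [(1.96 + 0.842) × 12.68 / 10.39]² = 23.39, close to the stated 25 per group. It uses no readmission rate, so it says nothing about this outcome.

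**Does a planned admission meet the definition?** The definition has two tests: a cardiovascular cause, and not one of the excluded causes. A pre-booked admission for angina passes the first. The two named exclusions, a cold and a tumor, are both non-cardiovascular, so the catch-all that follows them most naturally means further non-cardiovascular causes. On that reading the planned admission counts.

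**How large is the dilution?** Taken from the document: 40 per arm, two-sided 0.05. Assumed, because the document gives no rates: unplanned readmission of 20% (control) v 10% (intervention), and planned admissions with probability q, equal in both arms and independent of unplanned ones.

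The risk of any counted admission is p + q(1 − p). For q = 5%, control is 0.20 + 0.05 × 0.80 = 0.240 and intervention is 0.10 + 0.05 × 0.90 = 0.145. Power uses the normal approximation for two proportions with pooled variance under the null.

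| Planned q | Control | Intervention | Difference | Risk ratio | Power | n per arm for 80% power |
|---|---|---|---|---|---|---|
| 0 | 20.0% | 10.0% | 10.0 points | 0.50 | 0.237 | 199 |
| 2% | 21.6% | 11.8% | 9.8 points | 0.55 | 0.214 | 227 |
| 5% | 24.0% | 14.5% | 9.5 points | 0.60 | 0.187 | 270 |
| 10% | 28.0% | 19.0% | 9.0 points | 0.68 | 0.155 | 348 |

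Exact binomial enumeration for q = 0, 5% and 10% gives 0.247, 0.191 and 0.157 for the uncorrected chi-square test, and 0.162, 0.130 and 0.107 for Fisher's exact test.

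Other assumed base rates, with q going from 0 to 10%:

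- 10% v 5%: power falls from 0.132 to 0.077.
- 30% v 15%: power falls from 0.360 to 0.257.

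The difference is multiplied by (1 − q), so its sign cannot change.

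**What does the window do?** Suppose 20% v 10% is the 24-week risk and the hazard is constant. The 12-week risks are then 1 − √0.80 = 10.6% and 1 − √0.90 = 5.1%. Expected events are 40 × 0.20 = 8 v 40 × 0.10 = 4 by week 24, but about 4.2 v 2.1 by week 12. By the same formula, power is 0.237 at week 24 and 0.144 at week 12. On these assumptions, the choice of window matters at least as much as planned admissions do.

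**The case against.** The document never says that planned admissions are counted. The exclusion list ends in an open phrase that could be read to remove them, and a booked check-up is not clearly caused by a listed condition. This is fair. But if that was the intention, whoever classifies admissions cannot tell so from the text, and for a primary outcome that is itself a reason to clarify it.

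The 3 months of telephone follow-up may simply mean the period after the intervention, since Table 1 heads visit 9 as three months after the trial. That is possible, but readmission is also collected at visit 8, and neither visit is made primary.

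The size rests wholly on assumed rates. With planned admissions at 2%, power only moves from 0.237 to 0.214, and it is low before any planned admission is added. Both points stand.

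Two stronger readings are tempting, and the document supports neither:

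- A reader might infer that a patient who dies without readmission is scored as a success. No section says so. Statistical analysis fixes neither a denominator nor a rule for death. Withdrawal criteria says "The subjects who are withdrawn after randomization will be followed up for outcomes" and invokes intention to treat, without mentioning death. A death could be treated as an event, a non-event or missing, and a fuller protocol or analysis plan may settle this.
- A reader might infer that the definition could turn the result round. In every scenario above the direction is unchanged.

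**Conclusion.** The point holds as a matter of definition. A primary outcome is defined by cardiovascular cause alone, so on a literal reading it takes in admissions scheduled by index discharge. Its window is stated in two ways, with no primary time point.

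The effect is dilution. Under 20% v 10% and 40 per arm, it ranges from small (power 0.214 with 2% planned) to about a third of the power (0.155 with 10% planned, against 0.237 with none). These figures assume equal, independent planned admissions in both arms. None of the rates comes from the document, so the true size is unknown.

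The handling of death is not an error in the plan. It is worth reporting openly because one patient is 1/40 = 2.5 percentage points of an arm.

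**What to change.** Amend the readmission paragraph under Primary outcome measure:

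- Count the first unplanned cardiovascular readmission, from index discharge to one stated primary time point. Visit 9 (week 24) would suit, with week 12 as secondary.
- State that admissions scheduled by index discharge do not count.
- Record planned yes/no at the existing follow-up contacts, and have each admission classified by the outcome evaluators, whom the Blinding section already describes as blinded.
- Report deaths by arm beside readmission, with a sensitivity analysis that counts death as an event. Replacing the primary outcome with a composite is not needed, and would bring in non-cardiovascular deaths although the definition deliberately leaves out non-cardiovascular admissions.

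The cost is one extra form field and a short amendment by the route under Protocol amendments. Slightly fewer admissions will be counted. Trial status reports 20 participants already recruited, so planned status must be established for them too, and the change should be dated and made before any comparison by arm.

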#### Secondary outcome measure

Psychological capital: The positive Psychological Capital Questionnaire (PPQ) is used to evaluate the patient’s positive psychology. The questionnaire was revised by [name] et al. [33] of Nankai University on the positive psychological capital questionnaire compiled by Lutas et al. The questionnaire includes 26 items, Cronbach’s *α* coefficient is 0.92, and Cronbach’s *α* coefficient of each dimension is 0.81, 0.76, 0.75, and 0.78, respectively. The higher the score, the better the psychological capital. It will be measured at visits 1, 8, and 9.Subjective well-being: The General Well-Being Scale (GWB) is mainly used to evaluate the subjective well-being of patients. The scale was amended by Duan [34], a Chinese scholar, on the basis of Fazio. The scale includes 18 items, and the higher the score, the stronger the subjective well-being. The internal consistency coefficient of the scale is 0.91 for males and 0.95 for females. The internal consistency coefficient of the retest is 0.85, and the correlation coefficient between the subscale and total scale is 0.56–0.88. The subjective well-being score will be measured at visits 1, 8, and 9.Clinical indicators: Clinical indicators will be followed up by researchers through WeChat or telephone to collect relevant clinical laboratory indicators of patients in 3 months, including BP, blood lipid, blood glucose, BMI, etc. The clinical indicators will be collected at visits 1, 8, and 9.

#### Safety outcome measure

The safety assessment will be performed for all subjects who have been randomized and recorded positive events more than once. The subjects’ vital signs and general physical status will be examined at every visit. All participants will be required to report any adverse events (AEs) that occur during the trial of visits 2, 3, 4, 5, 6, 7, 8, and 9. All AEs that occur after the start of this trial should be recorded in the case report form, regardless of whether they are related to positive event recording or not. All AEs will be evaluated for causality.

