## Methods

### Study design and setting

This is a randomized controlled trial, which will be conducted in the Department of Cardiology, the First Affiliated Hospital of Soochow University. A written informed consent will be obtained from each individual by the researcher after the individual has received a sufficient explanation and period of time in which to make a thoughtful decision. All the patients will be randomized 1:1 into the intervention group (*n* = 40) or the control group (*n* = 40). The intervention group is given 3-month positive event recording intervention on the basis of conventional nursing, while the control group received conventional nursing, and both groups will be followed up for 3 months at the end of the intervention. The Cardiovascular Medicine Department of the First Affiliated Hospital of Soochow University is currently the largest cardiovascular disease diagnosis and treatment center in South Jiangsu Province, China. It has 180 beds, four cardiac catheterization rooms with advanced equipment, and a cardiac supersonic room and cardiac function room. Annually, an average of 5000 open-heart surgery candidates and 400 emergency operations are treated in the department. The protocol design is based on the Consolidated Standards of Reporting Trials (CONSORT) guidelines and Standard Protocol Items: Recommendations for Interventional Trials (SPIRIT) checklist (see Additional file 3). Figure 1 presents a schematic flow diagram of the study.

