#### Intervention

After randomization, the patients in the control group will receive conventional nursing, and the patients in the intervention group will record positive events for 3 months in addition to conventional nursing, that is, once a week for 12 weeks. Each patient in the intervention group will be assigned a notebook to record positive events and a health education manual. The specific implementation plan is as follows.

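### The safety set is defined by an activity that only the intervention group performs, so as written it contains no control patients and omits intervention patients with fewer than two recordings

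*Protocol article*

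**What the plan says.** The safety population is fixed in the protocol article under Safety outcome measure: "The safety assessment will be performed for all subjects who have been randomized and recorded positive events more than once".

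The Intervention section shows who records: "the patients in the control group will receive conventional nursing, and the patients in the intervention group will record positive events for 3 months". The materials follow the same split: "Each patient in the intervention group will be assigned a notebook to record positive events and a health education manual". The Control group section describes education, a discharge manual and follow-up calls, and contains no recording task.

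The sentences that follow the population rule in Safety outcome measure are not limited by arm or by recording: "All participants will be required to report any adverse events (AEs) that occur during the trial", and "All AEs that occur after the start of this trial should be recorded in the case report form", whether or not an event is thought to be related to the recording. Table 1 schedules adverse event monitoring without separating the groups. Withdrawal criteria says that patients withdrawn after randomisation are still followed for outcomes and that the data are analysed by intention to treat.

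**The concern.** A safety set is often defined by exposure to the study treatment. That works when both arms receive something that can be counted, such as active drug and placebo. Here the control arm receives nothing that meets the condition, so an exposure rule removes the comparator.

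Two things are at stake. First, the Background section says that some patients remain at risk of major cardiovascular events after PCI. An adverse event rate from the intervention arm alone cannot separate an effect of the recording programme from the underlying disease. The plan also asks for every event to be assessed for causality, which is harder to judge without a control rate.

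Second, the rule selects on what happens after randomisation. Withdrawal criteria lists failure to complete in connection with serious adverse events and complications as a reason for withdrawal. An intervention patient withdrawn for such an event before a second recording would leave the safety set because of the kind of event that the set is meant to capture.

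**Working it through.** The plan gives no size for the safety set, so there is no figure of its own to reproduce. The count follows from the definition.

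**Inputs**

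- Allocation: "All the patients will be randomized 1:1 into the intervention group" or the control group, 40 in each (Study design and setting).
- Condition for entry: randomised, and at least two recordings (Safety outcome measure).
- Who records: the intervention group only (Intervention; Control group).
- Number of intervention patients with zero or one recording: not given. Call it *k*.

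**Count by arm**

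- Control: no recording task, so 0 of 40 qualify.
- Intervention: 40 − *k* qualify.
- Safety set: 0 + (40 − *k*) = 40 − *k*, so at most 40 of 80.
- Excluded: 80 − (40 − *k*) = 40 + *k*, so at least 40 of 80 (40/80 = 50%).
- With all randomised patients by assigned group: 40 against 40.

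The zero in the control arm does not depend on *k*, nor on whether a recording means a weekly session or a single entry. Relaxing the threshold to one recording would also leave it at zero.

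**The passages side by side**

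| Place | Who is covered |
|---|---|
| Safety outcome measure, first sentence | Randomised patients with at least two recordings |
| Safety outcome measure, reporting of adverse events | All participants |
| Table 1, adverse event monitoring | No split by arm |
| Withdrawal criteria | Withdrawn patients followed up; intention to treat |

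The last three rows cover every randomised patient; only the first does not. Data would be collected on everyone, and at least half of the patients would then be removed by the population rule.

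**Start of monitoring.** The text of Safety outcome measure lists adverse event reporting from visit 2 to visit 9. Table 1 marks it from visit 3 (week 1) to visit 9. Any rewrite of the safety paragraph has to settle this difference.

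**The case against.** The strongest reply is that the harm is limited, and much of that reply stands.

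- **The data are not lost.** A reader might infer that the trial can make no between-group safety comparison at all. The documents do not support that. Adverse events are to be reported by all participants and entered in the case report form, so the comparison is barred only inside the set as defined.
- **Some harms are compared elsewhere.** Cardiovascular readmission and anxiety are primary outcomes and are not restricted to patients who record. This is partial cover: readmissions for other causes are excluded from that outcome, and events that do not lead to admission are not counted in it.
- **The loss of early risk time is easily overstated.** The programme is described as weekly ("that is, once a week for 12 weeks"), so one might infer that a second recording cannot exist before week 2 and that the first week of risk drops out. Table 2 asks for three events in week 1, and patients keep a daily log of their recordings, so the threshold could be met in week 1 if entries are counted. Patients who qualify later also keep their week 1 events. The rule drops patients; it does not drop time for those who stay.
- **The number of early stoppers is unknown.** The 20% loss in the sample size section covers loss in general and says nothing about patients with fewer than two recordings.
- **Safety is not a stated objective**, and the intervention is a writing exercise added to usual care.

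These points lower the severity. They do not rescue the sentence. The article states the population itself, so this is not a detail left to an unseen analysis plan or lost in condensing a longer document.

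**Conclusion.** The definition is wrong as written. It yields 0 of 40 controls and at most 40 of 80 randomised patients, and it leaves out intervention patients with zero or one recording. It contradicts the all-participant reporting in its own section and the follow-up of withdrawn patients under Withdrawal criteria.

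The control count rests only on the stated allocation and on the recording task belonging to one arm. The direction of any bias in the intervention arm rests on an assumption: that patients who stop early include some who stop because of an event. Withdrawal criteria makes this plausible but gives no rate, so the most that can be said is that harm may be understated.

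This should be fixed. It does not affect the primary estimates, the sample size or the error rates, and it is not a reason to doubt that the adverse event data will be collected.

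**What to change.** Replace the first sentence of Safety outcome measure with:

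> The safety set comprises all randomised patients, analysed by assigned group, with adverse events tabulated by group.

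In the same edit, reconcile the first visit for adverse event reporting between that section (visit 2) and Table 1 (visit 3).

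The cost is one sentence and one alignment of text and table. The set becomes 40 against 40, and no new data collection is needed beyond the all-participant reporting already planned. The change would go through the process under Protocol amendments. If a description of events among patients who did record is wanted, it can be given as a supplementary table for the intervention arm, labelled as such.

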#### Compliance monitoring and management

The researchers will collect the recording logs of the patients after 2 weeks of positive event recording for the purpose of calculating compliance. The compliance rate (%) = [continuous recorder as required/total number of interventions] × 100%. Only when the compliance is ≥ 70%, the research will continue; otherwise, find out the reasons and carry out scheme rectification.

#### Sample size calculation

Calculated according to the formula of sample size estimation based on the comparison of the mean of two independent samples [35]: *n*_1_ = *n*_2_ = 2[(*Z*_*α*_ + *Z*_*β*_)*σ*/*δ*]^2^ + *Z*^2^_α_, *σ* is the standard deviation, *δ* is the difference between the two population means, *n*_1_ and *n*_2_ are the required contents of the two samples, respectively, and *Z*_*α*_ and *Z*_*β*_ are *Z* values corresponding to the type I error probability and the type II error probability, respectively. At bilateral *α* = 0.05, power = 0.8, *Z*_*α*/2, ν_ = 1.96, *Z*_*β, ν*_ = 0.842, *σ* = 12.68, and *δ* = 10.39, the sample size for each group is 25 cases. Considering the 20% sample loss rate and other factors, the total number of samples is expected to be 80.

